#### Transfusion datasets

2.7.1

The Winpath system includes variables relating to G&S blood sampling and rejection, all blood units issued, and blood units transfused. BloodTrack Manager gathers electronic data regarding the use of PDAs, blood fridges, and BloodTrack kiosks. Incidents relating to non‐conformances or near misses relating to transfusion were collected through DATIX, that is, the Trust's incident reporting and risk management software. Adverse events relating to transfusion were collected through the national hemovigilance scheme. We applied the same data collection strategy across the four hospitals, that is, with the same variables extracted from the four datasets and the same time period applied.

#### Process mapping dataset

2.7.2

The process mapping dataset provides information about the time spent by clinicians in each step of the transfusion process. A structured data collection approach was used to map the transfusion process across the four hospitals within Barts Health NHS Trust. Clinician‐level time spent data were collected using a standardised audit form, a time‐in‐motion method, and a stopwatch to record process durations systematically. A data collection form was developed to capture the clinician time spent in hospital wards and staff time spent in the laboratories for blood transfusion.

#### Health Economics Inventory dataset

2.7.3

Two Health Economics Inventory forms were developed for the evaluation study. One form was applied in the staff training survey. Every clinician in this study was invited to complete the Health Economics Inventory form after she/he completed the BETC training. The form collected clinician‐level data on training duration, job title, years of experience in the current job, and feedback on the BETC system. The other form was used to collect data on costs for PDA devices and mobile printers, licence/software costs, and BETC system maintaining costs; material and consumable costs for G&S sample collection and labelling; salaries for BETC implementation staff and proportional salaries for two Transfusion Practitioners on the traceability task.

Figure 2 shows the linkage between outcome measures, proxies for outcome measures in various datasets, and the data sources.

**FIGURE 2 tme70002-fig-0002:**
[figure not shown]
Linking data sources with outcome measures for the evaluation of BETC implementation.

### 
Statistical analysis

2.8

#### Benefits to patients within the evaluation period

2.8.1

Regression based time‐series intervention analyses will be applied to evaluate the impact of BETC implementation on the number and rate of mislabelled samples at hospital ward level.^19^, ^20^ The analysis will reflect three key features of the BETC implementation, that is, staggered, adopted gradually, and non‐randomised. We will conduct descriptive analyses to summarise the other four outcome measures on benefits to patients at the hospital and year level.

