The BETC implementation at the four hospitals adopted a non‐randomised, staggered, multi‐phase strategy. The time horizon for the evaluation is 36 months. It includes a 12‐month pre‐implementation period (May 2022 to April 2023) and a 24‐month implementation period (May 2023 to April 2025). The implementation includes three phases:Pre‐Pilot (May 2022 to April 2023): This phase focused on site readiness, addressing all IT requirements for the use of the new system in clinical areas, and preparing training material to accommodate BETC integration.Pilot: The pilot was performed in the Haematology Day Units (HDU) at four hospitals. It allowed the project team to identify and resolve any unforeseen issues that had not been picked up in the pre‐pilot stage. The HDUs were chosen due to the high volume of pre‐planned blood transfusions.Full roll‐out: The main BETC implementation was phased out starting from Hospital 1 (July to November 2023), followed by Hospital 2 (December 2023 to March 2024), Hospital 3 (April to October 2024), and Hospital 4 (November 2024 to April 2025). After the completion of the roll‐out at each hospital, there was a three‐week evaluation period.

The principles of the implementation phases were the same across four hospitals, starting with HDU, followed by clinical wards, and then emergency clinical areas (i.e., the A&E department and theatres). The main part of the implementation included training clinicians on how to use the electronic devices (i.e., PDA and mobile printer) for steps 1 and 9. When 80% of clinical staff were trained in a clinical ward, electronic devices were released to the ward for use. Simulation training videos were developed and made available on the Trust intranet for staff to access. Dummy wristbands and dummy blood units were created for demonstration and to make the staff training reflect real practice as much as possible. After practical training, a competency assessment was obtained from all staff via an interactive PDF document, which included questions to consolidate learning and reinforce key points of the training that had been received.

By the end of the full roll‐out phase, we expect all wards to use the devices for transfusion. Some wards might have started using PDAs for transfusion during the full roll‐out period. We collected data for the PDA uptake at the ward level throughout the 24‐month implementation period.

### 
Study participants

2.5

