The target population was (a) any patient who has received a blood transfusion for any reason at four hospitals, (b) any patient who had G&S blood samples taken for compatibility testing for any clinical reason during the evaluation period, (c) all clinical staff involved in taking G&S blood samples or administering blood units to patients at four hospitals, and (d) supervisors who delivered the BETC training sessions to clinicians.

### 
Outcome measures

2.6

A summary of outcome measures, definitions, and data sources are reported in Table 1. Benefits to patients will be measured by the reduction in transfusion‐related errors, as proxied by the following five outcomes:Number and rate of mislabelled samples*.Number and rate of wrong blood in a tube*.Number and rate of patients who receive wrong blood due to errors related to bedside checks**.Number and rate of patients who are misidentified at the point of transfusion**.Number and rate of wrong blood units collected from the fridge due to errors related to bedside checks.

**TABLE 1 tme70002-tbl-0001:** Outcome measures for the evaluation of BETC implementation.

Outcome measures	Definitions	Data sources
Measures for benefits to patients		
Mislabelled samples	Samples contain incorrect information of the patient	Winpath, BloodTrack Manager
Wrong blood in a tube	A G&S sample contains blood from the wrong patient	Winpath, BloodTrack Manager, national hemovigilance scheme
Patients received wrong blood due to errors related to bedside checks	Administration of an incorrect blood unit to a patient due to failure in verifying patient identity and blood group compatibility	DATIX and national hemovigilance scheme
Patients are misidentified at the point of transfusion	A patient is incorrectly identified before receiving a blood transfusion	DATIX and national hemovigilance scheme
Wrong blood units collected from the fridge due to errors related to bedside checks	Incorrect blood units from storage due to failures in verifying patient details and blood group compatibility	DATIX and national hemovigilance scheme
Measures for clinician time saved		
Mislabelled samples	Time spent on G&S sample collection, labelling, analysis and reporting.	Process mapping
Wrong blood in a tube	Time spent on G&S sample collection, labelling, analysis, reporting.	Process mapping
Manually labelling blood samples	Time spent on writing patients' details for G&S labelling	Process mapping

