#### Cost savings within the evaluation period

2.8.2

Cost savings will be quantified by the monetary value of reduction in (1) clinician time used for completing transfusion‐related tasks and (2) transfusion‐related material and consumable use. We identified seven sources of savings for clinician time and two sources of savings for material and consumable use, as reported in Table 1.

For six (out of seven) sources of clinician time saving associated with BETC implementation, we will estimate the amount of time saved from each source by combining the time saved from one transfusion to the number of relevant transfusions. These will then be converted to monetary value by applying the hourly rate of clinicians.^21^, ^22^ Costs will be presented at 2023/24 level. For traceability, the monetary value of clinician time saved will be estimated by the proportion of salaries for two Transfusion Practitioners in Barts Health NHS Trust for their time spent on supporting the traceability of transfusions under the manual transfusion system. Regarding the two sources of cost savings in material and consumable use, for each source, we will identify and then quantify the material and consumable use items saved from one transfusion, followed by converting the quantities to monetary value by applying the unit cost for each item, and finally to estimate cost savings by combining monetary value from one transfusion to the number of relevant transfusions.

During the 2‐year implementation period, the PDA uptake did not reach 100% for many wards. Therefore, we will report two types of annual cost savings, that is, actual savings and potential savings when the maximum PDA uptake is achieved.

#### 
BECT implementation and staff training costs

2.8.3

We will report the actual implementation costs occurred at the Trust and year level. The costs include salary for implementation staff, costs for software licences, PDA hardware maintaining and software support fee, costs for PDA devices and mobile printers. Training costs for clinicians to learn how to use the PDA device will be calculated at clinician level by applying clinicians' hourly rate to the time spent on training sessions.

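### Four of the five patient-benefit outcomes are tabulated by hospital and undefined year, so most implementation-period cells mix months before, during and after roll-out; each hospital's own roll-out periods would be cleaner

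*Protocol article*

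**What the plan says.** Section 2.6 makes a reduction in errors the measure of patient benefit: "Benefits to patients will be measured by the reduction in transfusion‐related errors, as proxied by the following five outcomes". Section 2.8.1 then treats the five outcomes in two ways.

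- **Mislabelled samples** get a time-series regression to "evaluate the impact of BETC implementation on the number and rate of mislabelled samples at hospital ward level".
- **The other four** are wrong blood in a tube, wrong blood received, misidentification at transfusion, and wrong unit collected from the fridge. For these: "We will conduct descriptive analyses to summarise the other four outcome measures on benefits to patients at the hospital and year level".

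Section 2.4 gives the calendar. On the 36-month window: "It includes a 12‐month pre‐implementation period (May 2022 to April 2023) and a 24‐month implementation period (May 2023 to April 2025"). Full roll-out ran in consecutive blocks, "starting from Hospital 1 (July to November 2023), followed by Hospital 2 (December 2023 to March 2024"), then "Hospital 3 (April to October 2024), and Hospital 4 (November 2024 to April 2025"). Before that, "The pilot was performed in the Haematology Day Units (HDU) at four hospitals", with no dates given. Section 2.8.2 adds: "During the 2‐year implementation period, the PDA uptake did not reach 100% for many wards".

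**The concern.** A reduction is read by comparing a period without the system to a period with it. The chosen cell, one hospital in one year, does not follow the date on which each hospital changed over. A cell that holds months from both sides of that date belongs to neither period, and its rate is a weighted average of the two.

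Section 2.8.1 does not say whether a year means an evaluation year (May to April), a calendar year or a financial year. The choice changes which cells are mixed and how long they are.

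At stake is how clearly these error outcomes can be read. Section 2.8.4 says that transfusion-related mortality and serious morbidity are rare and that little immediate effect on them is expected, so the error outcomes carry the safety evidence within the window. Wrong blood in a tube is also a listed source of time and material savings in Table 1, and a mixed hospital-year rate does not show the rate under the new system.

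**Working it through.** The protocol gives no event rate, effect size or sample size for these four outcomes, so there is no figure of its own to reproduce. The check has two parts: a month count, which uses only the dates in section 2.4, and an illustration of dilution, which needs assumptions.

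**1. Month count.** Each of the 36 months at each hospital is classed as before, during or after that hospital's full roll-out. Entries are before/during/after.

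| Hospital | Year 1 (May 2022–Apr 2023) | Year 2 (May 2023–Apr 2024) | Year 3 (May 2024–Apr 2025) | Total |
|---|---|---|---|---|
| 1 | 12/0/0 | 2/5/5 | 0/0/12 | 14/5/17 |
| 2 | 12/0/0 | 7/4/1 | 0/0/12 | 19/4/13 |
| 3 | 12/0/0 | 11/1/0 | 0/6/6 | 23/7/6 |
| 4 | 12/0/0 | 12/0/0 | 6/6/0 | 30/6/0 |

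Mixed cells in years 2 and 3: Hospitals 1, 2 and 3 in year 2, and Hospitals 3 and 4 in year 3. That is 5 of 8. Hospital 3 in year 2 is mixed by one month only, which leaves four materially mixed cells.

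The implementation period holds 4 × 24 = 96 hospital-months:
- before: 2 + 7 + 11 + 12 + 6 = 38 (40%)
- during: 5 + 4 + 1 + 6 + 6 = 22 (23%)
- after: 5 + 1 + 12 + 12 + 6 = 36 (37.5%)

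**2. Other definitions of year.** Calendar years give 5 mixed cells of 16, with part-years of 8 months (2022) and 4 months (2025). April-to-March years give 4 of 16, with a first year of 11 months and a last year of one month. No definition removes the mixing, and these two also make raw counts non-comparable between years.

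**3. Dilution.** Assumptions: exposure rises linearly from 0 to 1 over the roll-out months (taken at mid-month), uptake is full afterwards, activity is constant, and there is no pilot effect. A roll-out lying wholly inside a year then contributes half its months as exposed.

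Mean exposure e = (exposed month-equivalents) / 12. Apparent rate ratio against year 1 = 1 − (1 − true ratio) × e.

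| Cell | e | True ratio 0.50 | True ratio 0.20 |
|---|---|---|---|
| H1 year 2 | (2.5 + 5)/12 = 0.625 | 0.69 | 0.50 |
| H2 year 2 | (2 + 1)/12 = 0.25 | 0.88 | 0.80 |
| H3 year 2 | (0.5/7)/12 = 0.006 | 1.00 | 1.00 |
| H3 year 3 | (3.5 − 0.07 + 6)/12 = 0.786 | 0.61 | 0.37 |
| H4 year 3 | 3/12 = 0.25 | 0.88 | 0.80 |
| H1 and H2 year 3 | 12/12 = 1 | 0.50 | 0.20 |

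Both true ratios are illustrative; neither comes from the protocol.

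**The case against.** The plan calls these summaries descriptive and attaches no test or effect estimate to them. Reporting by hospital keeps the staggering visible. The Discussion says openly that hospitals will be at different stages of uptake, with Hospital 4 likely the lowest, and that full benefits will not be observed. In a condensed article, table layout and period definitions are often left to a fuller plan. All of this stands and lowers the severity. It does not remove the point, because the article itself names the grouping and that grouping does not follow the roll-out.

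Three stronger readings are tempting and should not be drawn.

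- **That any effect is diluted or unreadable, or that the table cannot show a before/after contrast.** On evaluation years, year 1 is wholly before at every hospital and year 3 is wholly after at Hospitals 1 and 2. Hospital 3 in year 3 has no pre-roll-out month. Hospital 4 in year 2, and in effect Hospital 3 in year 2, are sound before cells, where a ratio near 1.00 is correct.
- **That year boundaries explain everything.** Hospital 4 has no post-roll-out month under any grouping, because its roll-out ends with the window. Dilution from incomplete uptake would also survive re-tabulation.
- **That section 2.8.1 breaks its own promise to reflect staggered, gradual adoption.** That sentence follows the mislabelled-sample regression and is most naturally read as describing it. The Discussion speaks more broadly of addressing these design features, but its example is again mislabelled samples. There is no internal contradiction.

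**Conclusion.** The point holds as a weakness in the stated grouping. With evaluation years, 5 of 8 implementation-period hospital-years mix exposure (four materially), and 38 of 96 implementation hospital-months precede that hospital's full roll-out. These counts depend only on the section 2.4 dates and on reading the year as May to April.

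The apparent ratios of 0.69, 0.88, 0.61 and 0.88 depend on the assumed true ratio of 0.50 and the assumed uptake curve, and serve only to show scale. Lower real uptake would attenuate every exposed cell further, including those at Hospitals 1 and 2 in year 3. Pilot use in the Haematology Day Units would add some exposure to months counted here as before roll-out; its size cannot be judged without the pilot dates.

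Severity is low to moderate: a cheap improvement to a descriptive table, not a must-fix.

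**What to change.** In section 2.8.1, keep the four outcomes descriptive but change the grouping.

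- Tabulate events and matching denominators (G&S samples or units transfused, as the outcome requires) by each hospital's own before, during and after roll-out periods, instead of or alongside years. The lengths in months are H1 14/5/17, H2 19/4/13, H3 23/7/6 and H4 30/6/0.
- Give exact intervals for the rates.
- If years are kept as well, define the year.
- Classify Haematology Day Units from their own pilot start where that date is held.
- State that Hospital 4 contributes no post-roll-out month.

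A split by electronic versus manual handling is optional, and only where incident records allow it; the article does not show that DATIX or haemovigilance reports can be linked to device use.

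**Cost:** a change of wording and a re-tabulation using roll-out dates already known. The table becomes slightly more complex and its periods are unequal in length, so rates rather than raw counts must be compared.

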#### Cost savings within the evaluation period

2.8.2

Cost savings will be quantified by the monetary value of reduction in (1) clinician time used for completing transfusion‐related tasks and (2) transfusion‐related material and consumable use. We identified seven sources of savings for clinician time and two sources of savings for material and consumable use, as reported in Table 1.

For six (out of seven) sources of clinician time saving associated with BETC implementation, we will estimate the amount of time saved from each source by combining the time saved from one transfusion to the number of relevant transfusions. These will then be converted to monetary value by applying the hourly rate of clinicians.^21^, ^22^ Costs will be presented at 2023/24 level. For traceability, the monetary value of clinician time saved will be estimated by the proportion of salaries for two Transfusion Practitioners in Barts Health NHS Trust for their time spent on supporting the traceability of transfusions under the manual transfusion system. Regarding the two sources of cost savings in material and consumable use, for each source, we will identify and then quantify the material and consumable use items saved from one transfusion, followed by converting the quantities to monetary value by applying the unit cost for each item, and finally to estimate cost savings by combining monetary value from one transfusion to the number of relevant transfusions.

During the 2‐year implementation period, the PDA uptake did not reach 100% for many wards. Therefore, we will report two types of annual cost savings, that is, actual savings and potential savings when the maximum PDA uptake is achieved.

#### 
BECT implementation and staff training costs

2.8.3

We will report the actual implementation costs occurred at the Trust and year level. The costs include salary for implementation staff, costs for software licences, PDA hardware maintaining and software support fee, costs for PDA devices and mobile printers. Training costs for clinicians to learn how to use the PDA device will be calculated at clinician level by applying clinicians' hourly rate to the time spent on training sessions.

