**FIGURE 1 tme70002-fig-0001:**
[figure not shown]
Transfusion process steps under manual and BETC systems. Steps 1, 9 and 10 under the manual system will be replaced by the BETC.

PPI checks must be performed every time for steps 1 and 9. In the manual process, step 1 requires that labelling on the blood sample and the request form is handwritten, where the clinician is required to write the patient's full name, date of birth, hospital number, NHS number, date and time when the sample is taken, and provide his/her signature. For step 9, prior to blood administration, PPI must be performed by two nurses who are required to check that the patient's details on the wristband match those on the blood unit and the compatibility label that is attached to the blood unit. For step 10, clinicians must return the traceability tag attached to the blood unit from the ward to the laboratory, where an individual will enter this information in the transfusion electronic system—this confirms the fate of the unit and is called traceability.

### 
Intervention

2.2

The intervention consists of a portable handheld scanning device (or Personal Device Assistance [PDA]) and a mobile printer. For the sample labelling (step 1), the PDA obtains the patient's details electronically via scanning the patient's 2D barcode on the wristband, which is embedded with the patient's details from the patient's electronic record and, in doing so, supports PPI. The PDA then communicates via Bluetooth with the mobile printer to print the label, which is then attached to the blood sample. For blood administration (step 9), the device uses the same 2D barcode to obtain and verify the patient's details against the compatibility label attached to the blood unit. For traceability (step 10), information on the use of blood is transmitted electronically every time a unit is being transfused using the PDA. It should be noted that the BETC can only be used if patients wear wristbands; consequently, these devices will not be implemented in areas where this was not the case (e.g., the outpatient setting for group and screen [G&S] samples).

The routine clinical care of patients receiving transfusions or needing blood samples will not be altered for the purpose of this study.

### 
Theory of change

2.3

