Manually writing post‐administration documents	Time spent on recording transfusion details after blood administration	Process mapping
Having second nurse for blood administration	Time spent by second nurse for compatibility check	Process mapping
Completing traceability documentations	Time spent on documenting and tracking blood transfusion details	Health Economics Inventory
Spillover effect	Time saved from a whole blood transfusion process after implementing the BETC	Process mapping
Measures for savings from material and consumable use		
Mislabelled samples	Material and consumable costs for G&S sample collection and labelling	Health Economics Inventory
Wrong blood in a tube	Material and consumable costs for G&S sample collection and labelling	Health Economics Inventory

**In cases where outcomes 1 and 2 overlap, the events will be counted only once, under outcome 2*.

***Errors that occurred at the point of transfusion, will be counted as outcome 4. Other errors will be counted as outcome 3, that is, ‘errors related to bedside checks’*.

Two types of hospital cost savings, as the results of the BETC implementation, will be assessed.Clinician time saved: Time saving will be generated from six sources including time spent on (1) re‐sampling because of mislabelled samples, (2) re‐sampling because of wrong blood in a tube, (3) manually writing blood sample labels, (4) manually writing post‐administration documents, (5) having a second nurse for blood administration, and (6) completing traceability documentations. Also, the implementation of BECT on steps 1, 9, and 10 might generate a spillover effect to other steps, and as a result save clinician time further.Reduction in material and consumable use: Savings will be generated from re‐sampling because of (1) mislabelled samples and (2) having wrong blood in a tube.

### 
Data collection

2.7

Data will be collected from three sources: (1) transfusion datasets: electronic laboratory databases Winpath and BloodTrack Manager, hospital‐based incident reporting schemes (or DATIX), and reports submitted to the national hemovigilance scheme, (2) Process mapping dataset, and (3) Health Economics Inventory dataset. The process mapping and Health Economics Inventory datasets were developed specifically for this evaluation study.

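### Section 2.8.2 scales the labelling and re-sampling savings by a count of transfusions, although they arise per G&S sample labelled or per re-sample avoided

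*Protocol article*

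**What the plan says.** Section 2.8.2 states one method for every clinician-time source except traceability: the amount saved is obtained "by combining the time saved from one transfusion to the number of relevant transfusions" and then priced at hourly rates. Traceability has its own method: "For traceability, the monetary value of clinician time saved will be estimated by the proportion of salaries for two Transfusion Practitioners".

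For consumables the same section says the evaluators will "quantify the material and consumable use items saved from one transfusion", price those items, and finish by "combining monetary value from one transfusion to the number of relevant transfusions".

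Section 2.6 describes what these sources are. Its list of time sources begins with "1) re‐sampling because of mislabelled samples, (2) re‐sampling because of wrong blood in a tube, (3) manually writing blood sample labels". On consumables it says: "Savings will be generated from re‐sampling because of (1) mislabelled samples and (2) having wrong blood in a tube". Table 1 defines all of these by the work or materials of G&S sample collection and labelling.

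Section 2.5 lists, separately from transfused patients, "any patient who had G&S blood samples taken for compatibility testing for any clinical reason during the evaluation period". Section 2.3 attributes the re-sampling benefit to a lower rejection rate for G&S samples. Section 2.7.1 says that Winpath holds data on sampling and rejection as well as on units issued and units transfused.

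**The concern.** A saving is a saving per event multiplied by a number of events, and both factors must refer to the same event. Here the stated event is a transfusion, while several of the savings arise at sampling, and not every sample leads to a transfusion. One sample may also precede several units.

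Cost savings are one of the two outcome families in the abstract, and the discussion offers the results as support for wider NHS roll-out. If the sampling-related savings are scaled by transfusions, two things follow. Part of the activity that BETC changes is left out. In addition, the re-sampling savings are not anchored to the reduction in mislabelled samples, the one patient-benefit outcome for which section 2.8.1 plans a formal model.

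**Working it through.** The article states no cost-saving figure, so there is nothing to reproduce. The check matches each source under the transfusion rule to the event that generates the saving, using section 2.6, Table 1 and section 2.3.

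| Source under the rule | Event that generates the saving | Transfusion count fits? |
|---|---|---|
| Time: re-sampling, mislabelled | Re-sample avoided | No |
| Time: re-sampling, wrong blood in tube | Re-sample avoided | No |
| Time: writing labels by hand | G&S sample labelled | No |
| Time: post-administration documents | Unit administered | Yes |
| Time: second nurse | Unit administered | Yes |
| Time: spillover | Whole transfusion process | Yes |
| Consumables: mislabelled | Re-sample avoided | No |
| Consumables: wrong blood in tube | Re-sample avoided | No |

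Mismatches: 3 of 6 time sources and 2 of 2 consumable sources, so 3 + 2 = 5 of 6 + 2 = 8.

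**Label writing.** Let S be the G&S samples labelled with the PDA, T the transfusions, and m the minutes saved per label.
- Saving required: m × S.
- Saving under the stated rule: (minutes per transfusion) × T.
- The two agree only if minutes per transfusion = m × S / T, and that requires S to be known first.
- A patient sampled but never transfused adds 1 or more to S and 0 to T.

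**Re-sampling, time and consumables.** Let A be the re-samples avoided and c the time or cost of one re-sample.
- Saving required: c × A.
- The stated rule agrees only if the saving per transfusion = c × A / T. T then cancels, and the quantity needed is still A.
- Section 2.7.2 does not supply A: process mapping measures how long each step takes, not how often a re-sample is avoided.
- Counting transfusions that involved a mislabelled sample does not give A either. It counts errors that happened rather than errors prevented, and it misses re-bleeds in patients who are never transfused.

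**Direction.** Section 2.1 gives about 65,000 units to about 15,000 patients in 2022, or 65,000 / 15,000 = 4.3 units per transfused patient. If units are counted and one sample covers several units, T can exceed S for transfused patients. Samples from untransfused patients push S above T. The two effects oppose each other. S, A and the rejection rates are not given, so neither the sign nor the size of the net effect can be computed. The 4.3 is not an error factor; it shows only that units cannot stand in for samples without further information.

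**The case against.** The strongest reply is that the wording is loose and the intended calculation is sound. The rule is applied source by source and refers to relevant transfusions, which suggests a count that varies by source. Section 2.1 describes transfusion as a ten-step procedure whose first step is sample collection and labelling, so the word may stand for the whole pathway. Figure 2 links outcomes, dataset proxies and sources; it is not shown here and may name sample counts. A journal article may also leave the count for each source to a fuller document.

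Much of this stands. It means that a wrong calculation has not been shown. It does not rescue the sentence: section 2.8.2 sorts the sources by method, exempts only traceability, and repeats the transfusion rule for consumables that arise only from re-sampling. Even on the generous reading, a patient sampled but never transfused contributes no transfusion.

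Three stronger readings are tempting but unsupported.
- *The re-sampling savings will be inflated many times over.* This requires a full per-re-sample saving to be applied to every transfused unit. The article does not make that pairing, and any multiple would rest on assumed sample volumes and rejection rates.
- *Potential savings ignore areas without wristbands.* Section 2.2 already says devices will not be implemented there and gives "the outpatient setting for group and screen [G&S] samples" as an example. Maximum uptake most naturally means uptake where devices are deployed. At most this needs a clarifying phrase.
- *The economic analysis will disregard the effectiveness model.* The article is silent on the link, and silence does not show that the model will go unused.

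**Conclusion.** The point holds as a correction to a stated rule. The multiplier named in section 2.8.2 does not fit five of the eight savings to which it is applied, by the article's own account of how those savings arise. Taken literally, it omits G&S samples from patients never transfused and does not tie re-sampling savings to fewer rejected samples. It is suitable for post-administration documents, the second-nurse check and spillover.

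No size can be attached. The article gives units and patients transfused but no G&S volume, rejection rate, or time or cost per sample, and the bias could run either way. The conclusion rests on the text of section 2.8.2 as it stands. If Figure 2 or a fuller document already assigns sample counts to these sources, the fault is confined to the wording, and the sentence should be brought into line.

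**What to change.** In section 2.8.2, replace the single multiplier with one count per source:

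- (a) Label writing: G&S samples labelled with the PDA.
- (b) Mislabelling, time and consumables: mislabelled samples avoided, taken from the time-series model in section 2.8.1, with its interval carried through to the savings.
- (c) Wrong blood in tube, time and consumables: events avoided, from the descriptive comparison in section 2.8.1. The overlap rule under Table 1, which counts shared events once, keeps (b) and (c) from double counting.
- (d) Post-administration documents and second-nurse check: units administered with the PDA.
- (e) Spillover: stays per transfusion.

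An optional addition is a phrase saying that maximum PDA uptake refers to areas where the devices are deployed.

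**Cost.** Mostly wording. Winpath already holds sampling and rejection data, BloodTrack Manager records PDA use, and Table 1 adds the national haemovigilance scheme for wrong blood in tube. The article does not say whether PDA use is recorded separately for sampling and administration, so that should be confirmed for (a) and (d). The analysis takes slightly more work, and the mislabelling savings will carry a wider interval because they inherit the model's uncertainty.
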